
**Fig. 2 Fig2:**
[figure not shown]
Digital pre-disclosure education intervention. **a** Web pre-disclosure education intervention. **b** Chatbot (Chat 1) pre-disclosure education intervention

**Fig. 3 Fig3:**
[figure not shown]
Digital return of results (ROR) intervention

**Table 1 Tab1:** Digital pre-disclosure education intervention (website)

Module	Tier 1 Content (# screens)*	Tier 2 Content (# screens)	Tier 2 Videos**[minutes]
WELCOME/LANDING PAGE	NA	NA	NA
1: Introduction	-What is the Penn Biobank Return of Results Program? (2) -What to expect (overview of content and option to opt out) (1) -Option to speak with a person (1)		
2: Genetics Overview	-Genes and inheritance (7) -Genes and health risks (1)		-Basic genetics overview [1:19]
3: Types of results and health implications	-What types of genes and conditions could be found (1) -How can genes impact health? (1) -How might learning my research results help me? (1)	-More information on cancer genes (1) -More information on cardiovascular genes (1)	-How cancer genes affect health [1:46] -How cardiovascular genes affect health [1:08]
4: Research v. clinical testing	-Need for confirmation testing (1) -Research v. clinical testing (1) -Medical follow-up (1) -How costs of confirmation testing will be covered (1)	-More information on medical care options for cancer genes (1) - More information on medical care options for cardiovascular genes (1)	-Research v. clinical testing [1:52] -Medical care for cancer genes [0:51] -Medical care for cardiovascular genes [0:56]
5: Risks, benefits and limitations of receiving results	-Potential benefits of receiving results (1) -Potential limitations of receiving results (1) -Potential risks of receiving results (1)		-Benefits [0:16], limitations [0:46] and risks [0:36] of receiving results
6: Next steps	-Overview: What’s next? (1) -What happens after I receive my results? (2) -HIPAA/privacy (3) -How would you like to proceed? ^ (1) -Survey request (1)		
Optional Content		Glossary of terms	

The intervention is informed by the tiered-binned model for genetic education and informed consent and was reviewed with cancer genetics providers and experts in health disparities and health communication. Readability testing was completed for all content and modifications made to achieve a readability score of 9th grade or lower. The linear digital intervention includes six modules and optional videos. Participants can view modules for as long, and as many times as desired. They can also go back to previously viewed topics

*All pages offer “Ask for Help” option

**Videos include a genetic counselor explaining specific topics. Content in some videos are intentionally redundant to Tier 1 and Tier 2 content and designed to provide an alternative method for reviewing content for participants with different learning preferences

^Participants can choose to: (a) opt out of receiving results, (b) speak with a staff member/GC to make a decision, (c) acknowledge they have enough information and understand they will be contacted if something is found in their sample

Completing Tier 1 content takes 8–14 min; completing Tier 1 and 2 content (excluding videos) takes 11–17 min

**Table 2 Tab2:** Digital return of results (ROR) intervention

Module	Tier 1 Content (# screens)*	Tier 2 Content (# screens)
1: Welcome Page/ Instructions	-Overview and option to speak with a genetic counselor (1) -How to use this website (1) -Option to review education^ (2) -Option to review specific education items (1)	-Basic genetics^^ -How genes impact health^^ -Research v. clinical testing^^ -Genetic mutations and medical care^^ -Benefits [0:16], limitations [0:46] and risks [0:36]^^
2: Test Result	-Ready to receive your results? (option for more time or to speak with a GC) (1) -Genetic test result (1)	-Copy of test report
3: Explanation of Result:	- Implications if result is confirmed (2–3 screens based on gene^#^) -What does this mean for my relatives? (1)	-Risks and guidelines
4: Next Steps	-Need for confirmation testing and medical follow-up if confirmed (1) -FAQ for confirmation testing (1) -Are you ready for confirmation testing? (yes, send me a kit or no, I would like to speak with a person)	-PDF of clinical test result (confirmation testing) available for download once result is available

*All pages offer “Ask for Help” option

^If participants have not previously viewed the digital pre-disclosure education intervention they have to actively decline education on this screen. If they decline, they are provided a single screen with key points (minimum information)

^^refers to duplicate screens from education website

^#^Option to select Risks and Guidelines for females v. males for some genes

Completing Tier 1 content takes 1–5 min; completing Tier 1 and 2 content (excluding videos) takes 5–12 min

Three chatbots, delivered by SMS, are designed to increase completion of pre-disclosure digital education, receipt of results and confirmation testing (Table 3). The education chat (Chat 1) includes the same information as the digital pre-disclosure education intervention but accessible via an SMS text to provide a different modality for accessing this information. The results reminder chat (Chat 2) includes instructions for receipt of results via an SMS text, and the confirmation testing follow-up chat (Chat 3) includes information on confirmation testing along with an option to view the commonly asked questions accessible via an SMS text.

**Table 3 Tab3:** Chatbot

Chat	Purpose	Content Summary*	Reminders
1: Chat 1 (Education chat)	Chat 1 (education chat) offers a summary of BioBank’s plan to return research results if available and next steps, while also providing an option to opt out or request assistance from study staff.	Participants are provided with an external link to an interactive form which has similar education content represented in Table 1.	-Requires Self-enrollment to Way to Health platform by participant. -There are no reminders sent if the chat is incomplete.
2: Chat 2 (Results reminder chat)	Chat 2 reminds participants of communication being sent about available research results.	- Informs that there is a research result available to learn (1) -Confirm if participant has received study communication (yes or no) (1) -Offer to resend the communication by email or mail (2) -Importance of confirmation testing and process (2) -Study team contact information (1)	-Includes initial notification 7 days after letter 2 is sent, followed by three reminders on days 5, 23, and 53.
3: Chat 3 (Confirmation Testing Follow-Up)	Chat 3 follows up with participants proceeding forward with confirmation testing.	-Confirm if participant received clinical confirmation testing kit (yes or no) (1) -Offer to help if participant has not received the testing kit (2) -Confirm if participant has mailed clinical confirmation testing kit back to laboratory (1) -Importance of clinical confirmation testing and commonly asked questions (2) - Study team contact information and confirm that participant is ready to send kit back if they have not already (1) -Ask reason for not proceeding forward with clinical confirmation testing (1)	-Initial notification sent 7 days after confirmation testing kit is ordered, followed by 3 reminders on days 5, 23, and 53.

*All three chats are initiated with a text message that asks participants to confirm their identity and the option to switch off text messaging by replying “BYE” or asking for help from the research team at any point by replying “ASSIST”

The chatbots were initially developed and hosted through a HIPAA compliant external vendor (Invitae Gia Clinic Hub), but transitioned to an internal platform (Way to Health) in 2024

### Setting

Participants are English-speaking adults who enrolled in the Penn Medicine BioBank (PMBB), which links genomic data to electronic health record (EHR) phenotype data at the University of Pennsylvania. We reviewed whole exome sequencing (WES) for actionable variants in genes on ACMG SF v.3.0 - v3.3 [75–78]. Variants were eligible for return based on ClinVar germline classifications (pathogenic, likely pathogenic, or conflicting classifications that included ≥ 2 laboratory submissions of pathogenic/likely pathogenic) or truncating variants (PTVs) (nonsense, frameshift), excluding the last exon and the last 50 base pairs (bp) of the penultimate exon, in genes where PTVs are a disease mechanism. For autosomal recessive conditions, variants were reviewed for either homozygosity of a single variant, or two different variants both meeting eligibility for return. Selected variants were deemed ineligible if sequencing read depth was < 25, allele depth was < 5, or homozygosity for the reference allele.

### Study participants

#### Eligibility

Eligibility criteria include individuals who participated in Penn Medicine Biobank, who are 18 years or older, able to understand and communicate in English, have an actionable genetic mutation (“cases”) or have been selected as a procedural control participant, and who agreed to be re-contacted in the future or were not provided the opportunity to indicate a preference. Procedural controls allow participants to learn about the return of results program and opt out before notification of an actionable result. This step was felt to be particularly important for this study as the return of results is not a primary focus at the time of consent to the PMBB, and the types of results being returned and procedures for return have not been included at the time of the original PMBB consent.

Exclusion criteria include individuals who are noted to be deceased in the EHR, are identified as deceased after contact or who have withdrawn consent to the PMBB. We exclude subjects for whom there was evidence in the clinical record of already having received the same actionable result through routine care (e.g. clinical genetic testing).

#### Enrollment goals

Our enrollment goal for the primary non-inferiority aim (Aim 1) is 255 participants per arm. To achieve this goal, up to 2500 PMBB participants (cases and procedural controls) are expected to be contacted.

### Study steps (Fig. 1)

#### Notification of the option to decline ROR and pre-disclosure education

Eligible cases and procedural controls are sent the Step 1 Letter (e.g. opt-out notification letter) (Supplemental Fig. 1) by MyPennMedicine portal (MPM), encrypted email or mail. The letter advises potential participants of (a) the potential for researchers to identify actionable genetic research results, (b) that researchers will be returning these actionable results to individuals if such is identified in their research sample, (c) that they can elect to NOT receive these actionable results (by calling a number or via the digital intervention), and (d) that all participants will be provided the opportunity to speak with a genetic counselor to receive their results. The letter also includes a link to view the pre-disclosure digital education, and a link to education chat (Chat 1) along with a QR code directing to the same link for Chat 1. Letter 1 also includes a one-page information sheet describing key points of the study and a one-page educational FAQ about the Biobank ROR program (Supplemental Fig. 1).

Those who request to speak with a genetic counselor as an alternative (or in addition) to completing pre-disclosure digital education are scheduled for remote telehealth counseling in the home by either phone or videoconference.

#### Randomization

After at least 4 weeks, participants with an actionable finding (cases) who have not chosen to opt-out of receiving their results are randomized to receive their results by remote telehealth disclosure with a GC (Arm 1) or by a private ROR digital intervention (Digital-ROR) with the option to schedule a call with a GC at any time in the process (Arm 2). A permuted block design is used for randomization, stratifying by cancer or cardiovascular genes and sex.

Randomized participants are sent the Step 2 Letter by MyPennMedicine portal (MPM), encrypted email or mail informing them that an actionable genetic finding that could potentially impact their health has been identified (Supplemental Fig. 2). The letter includes how they will receive their actionable results (according to their randomization), the next steps for receiving results and that they can still elect to NOT receive results. Procedural controls do not receive the Step 2 Letter, but any who opt-out of results after the Step 1 Letter has their decision recorded in case they are found to have an actionable result with additional sequencing or analysis.

#### Disclosure of genetic research results

##### Arm 1 (remote telehealth disclosure with a genetic counselor)

Participants randomized to remote telehealth disclosure with a GC (Arm 1) are provided with a telephone number and email for contacting the research team to schedule their disclosure session. Appointments are offered within 1–2 days of contact, and participants can choose telephone or videoconference for their disclosure session. Participants who have not completed the pre-disclosure education (digital or chatbot) are directed to complete it, or decline it, prior to being scheduled for result disclosure with a GC. Genetic counselors use standardized pre-disclosure counseling checklists adapted from the RESPECT single-site study and utilized in our pilot study [79]. A printed genetic research result report is mailed or emailed (encrypted) to a verified email account to Arm 1 participants following completion of remote disclosure (Supplemental Fig. 3).

##### Arm 2 (digital-ROR)

Participants randomized to the digital return of results arm are provided access information to the digital intervention in the Step 2 Letter. Participants who have not completed pre-disclosure education (digital or chatbot) are directed to complete it, or decline it, prior to proceeding to the results page on the digital-ROR intervention. Participants are informed in the Step 2 Letter, that they can choose to schedule a disclosure session with a genetic counselor if preferred. They can also request a remote telehealth visit with a genetic counselor at any time (e.g. before or after receipt of results). Arm 2 participants will have the ability to print a results report directly from the digital-ROR intervention.

##### Non-response procedures

For both arms, multiple follow-up attempts are made by phone, verified email, letter, or Chat 2 to all participants who do not call to schedule their remote disclosure session or log on to digital-ROR to receive their results. The results reminder chat (Chat 2) includes an initial notification 7 days after Step 2 letter is sent, followed by three reminders on days 5, 23, and 53. Chat 2 includes ways the research team can resend the Step 2 letter to participants if they indicate their desire to receive it again by email or through mail. The research team also makes three phone call attempts to contact the participant. Participants who have exceeded these contacts and have not received their results or communicated their decision to opt-out of receiving results are sent a Closing Letter (Supplemental Fig. 4), reiterating the option to receive actionable results but that the study team will not continue to attempt to contact the participant. Contact information is provided and they are informed they can reach out to the study team in the future if they are interested in receiving their results.

#### Clinical confirmation testing

Participants who receive actionable research results are instructed that confirmatory testing in a Clinical Laboratory Improvement Amendments (CLIA) -approved lab is required prior to making any changes to their health care. All confirmation testing is completed through Ambry and costs are covered with research funds to eliminate real or perceived cost barriers to confirming results. Testing kits are mailed to the participant’s home with instructions for how to provide a sample. Once results are available, confirmation test results are provided according to the original randomization arm (e.g. by GC or uploaded to the digital-ROR intervention). Once results are confirmed, the clinical test report and summary of the return of actionable results are documented in the EHR.

Multiple follow-up contact attempts are made to participants who do not complete confirmation testing. Three phone call attempts are made by the research team, and a confirmation testing follow-up chat (Chat 3) is sent to all participants who do not complete confirmation testing. Initial chat notification is sent 7 days after confirmation testing kit is ordered, followed by 3 reminders. Participants who have not completed confirmation testing will receive a Confirmation Testing Closing Letter (Supplemental Fig. 4) to reiterate the importance of confirmation testing and invite them to reconnect with the program to complete this step.

#### Clinical genetics referral

All participants with clinically confirmed results are recommended to the appropriate clinical genetics program for expert clinical recommendations and to facilitate appropriate clinical care based on their genetic test result. The participant’s contact information is provided to these clinical teams to schedule the clinical visit. The number of contacts for scheduling is based on the standard clinical procedures for each of the clinical programs. For participants who are no longer local, information about the local clinical genetics program is provided.

Those who have not completed clinical genetics follow-up are provided a Clinical Follow-up Closing Letter, reiterating the importance of this clinical appointment and inviting them to reconnect with the program for assistance in getting a referral (Supplemental Fig. 4).

### Outcomes

#### Conceptual model

Understanding the outcomes of receiving genetic results will be critical to realizing the risks and benefits of returning actionable genetic research results. The effectiveness of returning genetic information is contingent upon successful behavior modification (e.g. performance of risk-reductive interventions and communication to relatives). Thus, our studies evaluating delivery innovations in genetic medicine have been informed by our conceptual model grounded in The Self-Regulation Theory of Health Behavior (SRTHB) [80–87]. SRTHB has been utilized in intervention-based research involving the study of health threats and behaviors [88–90]. It proposes that the reaction to and use of health information is the product of an individual’s understanding and the biopsychosocial impact of the risk and the health behavior. It emphasizes “common-sense” representations rather than medical or scientific definitions, and incorporates individual, biological, cognitive, emotional, familial and cultural experiences that might contribute to individual variability in outcomes [82, 91, 92]. The literature and our data support the hypothesis that cognitive (knowledge and perceptions), psychological (e.g. distress, uncertainty) and behavioral (risk reducing behaviors and communication to relatives) outcomes will be moderated by test result [93–96], cancer and cardiovascular history [94, 97–99], sociodemographic factors, e.g. education, race/ethnicity [94, 99–101], and cognitive and emotional factors, e.g. health literacy [102–104] (Supplemental Fig. 5).

Even after health-related interventions have proven effectiveness, many fail to translate into clinical settings [105, 106]. Thus, there is increasing recognition of the importance of evaluating and addressing barriers to implementation across diverse health care settings. The Consolidated Framework for Implementation Research (CFIR) provides an overarching theoretical framework to evaluate barriers, enhancements and adaptations to increase successful implementation of effective interventions and delivery adaptations [107]. We have included constructs from each of the 5 major CFIR domains as they relate to our return of results approach and eHealth delivery alternatives (Supplemental Fig. 5), which will be evaluated in our multi-stakeholder mixed-methods process evaluation. Evaluation of CFIR components is expected to identify patient, provider and system barriers and enablers of our return of results approach and increase future implementation in other research and health care settings [108–110]. 

#### Uptake of results and patient reported outcomes (aims 1 and 2)

Theoretically informed patient-reported cognitive, affective and behavioral outcomes of genetic services are collected at baseline (T0), 2–7 days post-disclosure (T1) and at 6 months (T2).

Knowledge of genetic disease (primary non-inferiority outcome) is evaluated at all time points (T0-T2) using an adapted version of the KnowGene Scale, a 16-item scale administered to patients after genetic testing and/or genetic counseling to measure their understanding of the health implications of genetic test results [111]. It includes health implications to oneself as well as relatives. This measure covers penetrance, actionability, limitations of current technology, and monogenic inheritance patterns. Items 3, 5, 13 and 15 were excluded as they are not relevant to return of actionable results. Additionally, 4 items evaluating understanding of the difference between research and clinical testing and utilized in the RESPECT2 study were added to create a final scale of 16 items. This adapted scale has had good internal consistency in our pilot and related studies (Cronbach’s α = 0.63–0.83) [79, 112]. Perceived risk of cancer and cardiovascular disease (T0-T2) is evaluated with a numerical scale (risk 0-100%) and an 5-point verbal scale (much lower than average risk to much higher than average risk) as utilized in our related studies. The 8-item Attitudes Toward Genetic Testing scale is assessed at baseline to understand perceptions of genetic testing and to assess informed choice in combination with genetic knowledge and decisions to proceed with testing, as previously utilized in the multi-dimensional measure of informed choice and our related research (Cronbach’s α = 0.73) [113–115]. *Reactions to genetic information* are assessed with multiple instruments that evaluate psychological distress, adjustment and satisfaction. (a) Disease-specific distress (primary non-inferiority outcome) is measured at all timepoints (T0-T2) using the 8-item version of the Revised Impact of Events Scale (RIES) [94, 116–121], evaluating intrusive and avoidant thoughts regarding cancer and cardiovascular disease separately. The 8 item scale has strong internal consistency in related studies and our pilot study (Cronbach’s α = 0.70–0.92) [122, 123]. (b) *General anxiety and depression* are assessed by the respective 4-item short Patient Reported Outcomes Measurement Information System (PROMIS) scales (Cronbach’s α = 0.88 and 0.86) [79, 124]. (c) *Satisfaction with genetic services* (T1 only) will be assessed with a 14-item satisfaction with communication scale, and adapted for telehealth and digital disclosure, evaluating participants’ experience with high internal consistency in our related studies (Cronbach’s α = 0.73–0.85) [112, 114, 125] (d) *Multidimensional responses to genetic testing*, including positive responses and uncertainty, are assessed at T1 and T2 using the 20 items from the Multi-dimensional Impact of Cancer Risk Assessment Questionnaire (MICRA) with strong internal consistency in our pilot study by subscales (Cronbach’s α = 0.77–0.85) [79, 126]. (e) Decisional regret (T1, T2) is assessed using with the 5-item validated Decision Regret Scale used in genetic studies [127, 128]. This scale has had strong internal consistency in our pilot study (Cronbach’s α = 0.86) [79]. *Use of genetic information* includes uptake of receipt of actionable research results and other health and communication behaviors. (a) *Uptake of research results (secondary non-inferiority outcome)* will be assessed as completion of a remote telehealth disclosure session with a GC (either arm) or as viewing results in digital-ROR (digital arm). Other secondary uptake behaviors include uptake of supplemental digital education (Aim 2a), assessed as completion of pre-disclosure digital education or Chat 1, actively opting-out of receipt of research results after the Step 1 or Step 2 Letter (Aim 2b), completion of confirmation testing, and completion of clinical genetics follow-up, either by documentation in the EHR or self-report by those who are no longer in the local area. (b) Risk reducing behavioral intention (T1 only) and performance (T2) will be assessed with a close-ended and open –ended items given a lack of established measures and the wide range of potential medical management options depending on the individual gene. General health status and risk modifying behaviors (e.g. diet, exercise, tobacco and alcohol use) will be assessed at baseline and at T2 with items utilized in BRFSS and related studies [73, 125, 129]. Additionally, gene-specific medical management or risk reducing screening and interventions will be abstracted from medical records. (c) Communication of genetic test results includes communication intent (T1 only) and performance (T2) assessed using a 3-item measure of intent and communication to assess intent to share genetic test results with health care providers, family members and other third parties utilized in related research [85–87]. 

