### Objectives

The goal of the RESPECT3 Study is to conduct a Hybrid Type 1 effectiveness-implementation study to evaluate digital delivery alternatives for pre-disclosure education and return of actionable genetic research results. Based on our preliminary data and related research, we include both digital pre-disclosure education interventions and a private web-based portal for return of individual research results as an alternative to result disclosure by a genetic provider. Additionally, the study incorporates three chatbots designed to increase completion of pre-disclosure education, receipt of results and clinical confirmation testing.

#### Specific aim 1

Our primary aim is to evaluate in a randomized study whether disclosure of actionable genetic results by a digital intervention (digital-ROR) provides non-inferior short-term and longitudinal outcomes (knowledge, psychological distress, health and psychosocial behaviors and costs) compared to remote telehealth disclosure by a genetic counselor (GC)(e.g. usual care).

#### Specific aim 2

Our secondary aims are to evaluate the uptake of supplemental digital education (offered through a digital intervention or a chatbot) among Penn Biobank research participants notified of the option to opt-out of receipt of actionable genetic research results (Aim 2a), to evaluate the frequency of opting-out of receipt of actionable genetic research results (Aim 2b) and to evaluate the impact of use of digital education on opting out of receipt of actionable results (Aim 2c).

#### Specific aim 3

Our third aim is to conduct a multi-stakeholder mixed-methods process evaluation to understand the potential moderators (e.g. intervention usage, sociodemographic factors, genetic test result) of short-term and longitudinal outcomes to understand who benefits more or less from digital education and digital return of results (Aim 3a), and to understand the facilitators and barriers to implementation of digital interventions for return of actionable genetic research results and recommendations for future adaptation and sustainability (Aim 3b).

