#### Aim 2 analyses

Estimation of the proportion opting out will constitute our primary Aim 2 analysis and estimation of the proportion with uptake of supplemental digital education will constitute our secondary Aim 2 analysis. We will also estimate 95% confidence intervals with the proportions. For our primary Aim 2 analysis, we will test whether the proportion opting out is 5% using a one sample binomial exact test. We will primarily assess the proportions opting out with respect to those who are evaluable (i.e., alive and who do not have returned mail). We will subsequently assess proportions among those evaluable and who have an actionable result (secondary analysis). We will also compare opt-out between cases and controls.

For our secondary Aim 2 analysis, uptake of digital education will be classified as (1) accessing digital education, and (2) completing digital education. Secondary outcomes of education uptake will include (3) the platform used (web or chatbot), (4) # of visits to digital education, (5) total time, and (6) accessing videos. We will describe secondary outcomes using means and standard deviations (e.g., time and # of visits) or proportions (e.g., accessing individual videos) as appropriate. To evaluate the impact of completing education on opting out, we will compare opt-out rates between those who do and those who do not access and complete digital education using Fisher’s Exact Tests (Aim 2c). In secondary analyses, we will use generalized linear models with appropriate link and family functions for Aim 2 endpoints (e.g., Poisson regressions for # of visits, linear regressions for baseline patient reported outcomes). We will enter confounders into the models. We will examine models separately for those who did and those who did not receive letter 1 or letter 2.

#### Sample size justification for aim 2

We anticipate an approximate 5% opt-out rate based on our pilot data. With at least 1250 participants (and up to 2500 participants), we will be able to test whether the rate is < 5% (null hypothesis) versus > 7.5% (alternative hypothesis) with 95% power and a 2.2% Type I error rate (one-sided), and the use of a one-sample binomial test.

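### Aim 2a education uptake has no cut-off at the Step 2 Letter, so the pooled proportion can mix response to the opt-out notice with a later prompt that only randomised cases receive

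*Protocol article*

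**What the plan says.** Specific aim 2 (Objectives) places Aim 2a among "Penn Biobank research participants notified of the option to opt-out of receipt of actionable genetic research results". Under Notification of the option to decline ROR and pre-disclosure education, the Step 1 Letter goes to cases and procedural controls and carries the links to the web education and to Chat 1.

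The Outcomes section scores "uptake of supplemental digital education (Aim 2a), assessed as completion of pre-disclosure digital education or Chat 1". Aim 2 analyses adds that "uptake of digital education will be classified as (1) accessing digital education, and (2) completing digital education", followed by platform, visits, time and videos. Neither section gives a time limit.

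After the Step 2 Letter there is a second prompt. Arm 1 participants without the education "are directed to complete it, or decline it, prior to being scheduled for result disclosure with a GC". Arm 2 participants "are directed to complete it, or decline it, prior to proceeding to the results page on the digital-ROR intervention". The footnote to Table 2 says that on the digital-ROR site "they have to actively decline education on this screen"; those who decline see one screen of key points. The Randomization section states that "Procedural controls do not receive the Step 2 Letter".

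Aim 2 analyses also plans separate secondary models by receipt of letter 1 or letter 2, and for Aim 2c a comparison of opt-out rates between people who do and do not access and complete the education.

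**The concern.** The uptake estimate should tell a biobank how many people use the education when a letter tells them they may opt out. As written, it pools a group given one offer with a group given two, and the second offer comes after a finding has been announced.

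Three records scored literally show the problem:

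- A control ignores the Step 1 Letter: score 0.
- A case ignores it in the same way, then completes the education when prompted before results: score 1.
- A case completes it in response to the Step 1 Letter: score 1.

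The first two people responded identically to the opt-out notice but score differently. The pooled proportion therefore depends partly on how many controls the study chose to contact. The access, visit, time and video measures share the problem.

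Aim 2c uses the same variable. People who complete at the second prompt were randomised, so by design they had not opted out at Step 1. Counting them as educated adds non-opt-outs to that group and can make education look as if it lowers opting out.

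**Working it through.** **The plan's own figure.** The article gives no target or precision for education uptake. Its only Aim 2 sample-size statement concerns opt-out (5% against 7.5%, n = 1250), and that reproduces: rejecting at 79 or more opt-outs gives an exact one-sided Type I error of 2.17% and power of 95.2%, against the stated 2.2% and 95%. The present point does not depend on it.

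**Inputs from the article**

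- Cases: 255 per arm, so 510 (Enrollment goals). Reading these as the randomised cases is an assumption; more randomised cases would enlarge the effect.
- Contacted: N = 1250 to 2500 (Sample size justification for aim 2). The case share is 510/2500 = 20.4% to 510/1250 = 40.8%.
- Share of cases who go on to results: r = 44% to 55% (the discouraging and promising rates in Sample size justification for aim 1), used as a proxy for reaching the second prompt.

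**Inputs assumed**

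- Uptake before the Step 2 Letter, equal in cases and controls: u = 10% to 50%.
- Share of not-yet-educated cases at the prompt who complete rather than decline: g = 0 to 100%.

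**Pooled uptake.** With a cut-off the proportion equals u. Without one it is u + (510/N)(1 − u) × r × g. For u = 30%, r = 55%, g = 50% and N = 2500, the excess is 0.204 × 0.70 × 0.55 × 0.50 = 0.039.

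| g | N = 2500 | N = 1250 |
|---|---|---|
| 0% | 30.0% | 30.0% |
| 25% | 32.0% | 33.9% |
| 50% | 33.9% | 37.9% |
| 100% | 37.9% | 45.7% |

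Over u = 10% to 50%, r = 44% to 55% and g = 25% to 100%, the excess runs from 1.1 points (N = 2500, u = 50%, r = 44%, g = 25%) to 20.2 points (N = 1250, u = 10%, r = 55%, g = 100%). At g = 0 it is zero.

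For comparison, the half-width of the 95% confidence interval at 30% is 1.96 × √(0.3 × 0.7/N): 1.8 points at N = 2500 and 2.5 at N = 1250.

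**Aim 2c.** Take a true opt-out rate of 5% unrelated to education, with u = 30%, r = 55%, g = 50%. The number moved into the educated group is 510 × 0.70 × 0.55 × 0.50 = 98.2, none of them Step 1 opt-outs.

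- N = 2500: educated 37.5/(750 + 98.2) = 4.4%; not educated 87.5/(1750 − 98.2) = 5.3%.
- N = 1250: educated 18.75/(375 + 98.2) = 4.0%; not educated 43.75/(875 − 98.2) = 5.6%.

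The gap is produced entirely by the scoring rule.

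**The case against.** Several objections carry weight.

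- **Completion is not forced.** A reader might infer that the results step compels the education. It does not: both arms may decline and still receive results. The later completions are prompted, and inflation is possible but not certain.
- **The Step 2 Letter also repeats the option to decline results,** and the opt-out outcome counts decisions after either letter. Uptake over the whole pre-disclosure process is thus a coherent quantity. But only randomised cases receive that letter, so pooling over everyone contacted still depends on the case mix.
- **No case-control contrast of education uptake is planned.** A reader might infer that the trial will report a spurious difference between cases and controls. The article plans that contrast for opting out only, so the effect is on the pooled proportion and on Aim 2c.
- **The window may sit in a fuller document.** It may. But the article itself sets the scoring rule, and in the same sentence gives timing for opting out and none for education. The rule as published admits completions at the second prompt.
- **The split by letter helps.** Only partly: it applies to secondary models and divides by receipt of a letter, not by when the education was done.
- **The size is assumed.** That stands. In particular, people who ignored the Step 1 Letter may seek results less often than cases overall, which would shrink the effect.

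**Conclusion.** The point holds in limited form. The Aim 2a rule has no cut-off at the Step 2 Letter, and only randomised cases receive the later prompt, so the pooled proportion can overstate response to the Step 1 notice and varies with the case-to-control ratio. The size cannot be fixed from the article: zero if all decline at the prompt, and several percentage points under plausible assumptions, often more than the sampling error. These figures rest on assumed values of u and g, on the overall receipt rate applying to people not yet educated, and on 510 randomised cases. Aim 1 is unaffected, and education uptake is a secondary, descriptive Aim 2 estimate. The change is worth making because it is cheap and alters a reported figure.

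**What to change.** - Make the headline Aim 2a estimate education accessed or completed after the Step 1 Letter and before any Step 2 Letter, in one window for cases and controls. The first 4 weeks after the Step 1 Letter fits, being the minimum interval before randomisation. Apply the same window to visits, time and videos.
- Report completion or decline after the Step 2 Letter as a separate outcome, for randomised cases only.
- In Aim 2c, classify education by what was done before the opt-out decision being analysed. People who complete at the second prompt then stay out of the educated group for Step 1 opt-out, while education done after the Step 2 Letter still counts for a later Step 2 opt-out.

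The cost is a wording change and a date filter. The article says individual use of the digital interventions is recorded throughout the study; that these records are dated, for both the website and Chat 1, is assumed. The downside is that voluntary Step 1 completions later than 4 weeks leave the headline figure, and reported uptake may be lower.
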